### Eligibility criteria

#### Inclusion criteria

Patients admitted to a participating ICU identified by the treating intensivist as having an expected total ICU LOS of 72 h or more are eligible. Patients must be enrolled within 48 h of their ICU admission and receive the first dose of the study drug on the day of enrolment.

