### Interventions

Eligible participants will be randomised to receive melatonin 4 mg or placebo at 21:00 for 14 consecutive nights or until ICU discharge, whichever occurs first. This will be given either orally or via nasogastric tube, depending on the circumstances. All concomitant care and interventions that are normal practice for the ICU or based on other trials are permitted.

A subset of 100 patients will also undergo two episodes of polysomnographic testing overnight on days 2–3 and days 5–7 of their ICU stay. This will occur only at the two primary sites: Sir Charles Gairdner Hospital and John Hunter Hospital.

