#### Sleep quality

Sleep quality will be measured by (1) daily patient/nurse-rated sleep assessment (Richards-Campbell Sleep Questionnaire) while in ICU [46] and (2) patient-rated sleep quality questionnaire after ICU discharge [47]. This will be performed from 2 to 14 days after ICU discharge with the timing dependent on the patient’s ability to participate. Patients unable to participate will be omitted.

A subgroup of 100 patients will undergo sleep quality assessments twice during their ICU stay using polysomnography. The hypothesis is that melatonin will increase the quality and quantity of sleep compared with placebo. These 100 patients will come only from either Sir Charles Gairdner Hospital or John Hunter Hospital. Patients included in the study at these sites will be sequentially allocated to the subgroup. Polysomnography will be done between days 2 and 3 and between days 5 and 7 of the ICU stay. For logistical reasons, we will have limited access to polysomnography. It will be available only from Monday through Thursday, and hence we have not been able to randomise patients to this investigation. It is expected that, by virtue of blinding and randomisation, approximately 50% of patients will be from the melatonin arm and 50% from the placebo arm. The polysomnography protocol and reporting have been standardised and agreed upon by senior sleep physicians at the two main centres. Patients will not be in a single room every time polysomnography is performed, because this is a pragmatic study and will reflect real-world conditions as much as possible. Many participating units do not have single rooms for all of their patients. The range of days is selected so that if patients cannot undergo polysomnography because of procedures, they could have it the following night. If polysomnography needs to be aborted, we will try to repeat it within that range of days. This will aid in the understanding of sleep patterns in the critically ill and the biological mechanisms through which melatonin may work.

Several parameters will be generated by the sleep studies. Two sleep experts involved in the study design have selected the following four variables as the most important (each will be a secondary outcome): (1) total sleep time, (2) sleep efficiency, (3) percentage REM sleep and (4) arousal index.

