### Participant timeline and recruitment

Patients will be screened on the morning handover for eligibility. Baseline data will be recorded on day 0. Patients will be assessed each day and have the primary and secondary outcomes recorded daily until ICU discharge or day 14 after enrolment. Patients will be seen on the ward between days 2 and 14 after ICU discharge to complete the sleep questionnaire. Patients who have been discharged home will be contacted by phone. Patients will be followed through their hospital stay to record ICU LOS, hospital LOS, and 28- and 90-day mortality. The trial assessment schedule is displayed in Table 1 and Fig. 1.

**Table 1 Tab1:** Time schedule of Pro-MEDIC enrolment, interventions and assessments

	Day 1	Day 2	Day 3	Day 4	Days 5–14	Days 2–14 post-ICU discharge	Hospital discharge	Days 28 and 90
Inf`ormed consent	X							
Demographic information	X							
Medical co-morbidities	X							
Psychiatric history	X							
Liver function tests	X				X (days 0, 5 and 10)			
CAM-ICU score	X	X	X	X	X			
CAM-S test (for patients found to be delirious)	X	X	X	X	X			
Record daily ICU interventions	X	X	X	X	X			
Record daily anti-psychotic and sedation use	X	X	X	X	X			
Record daily sleep aid measures	X	X	X	X	X			
RCSQ	X	X	X	X	X			
Use of physical restraints	X	X	X	X	X			
Physiotherapy participation	X	X	X	X	X			
Polysomnography		X			X			
Assessment of sleep quality						X		
ICU and hospital LOS							X	
Hospital discharge destination							X	
Mortality at 28 and 90 days								X

*Abbreviations: CAM-ICU* Confusion Assessment Method for the ICU, *CAM-S* Confusion Assessment Method for delirium severity, *ICU* Intensive care unit, *LOS* Length of stay, *Pro-MEDIC* Prophylactic Melatonin for Delirium in Intensive Care, *RCSQ* Richards-Campbell Sleep Questionnaire

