### Statistical methods

Analyses will be conducted on both intention-to-treat and per-protocol bases. All outcomes will be analysed for superiority (two-sided) and considered statistically significant at the 5% level. Baseline data will be recorded and analysed for imbalances between the treatment groups. The primary endpoint, percentage of delirium-free assessments, will initially be analysed using a Mann-Whitney *U* test to compare the two treatment arms. Subsequent supporting analyses will be carried out using a negative binomial model with adjustments made for number of assessments (accounting for withdrawals), important covariates and baseline data where appropriate. Secondary endpoints of any prevalence of delirium during the 14 days and duration of delirium from first onset will be analysed using a chi-square test with supporting analyses of binary and ordinal logistic regression, respectively, allowing adjustments for covariates. Sleep quality analysis based on the Richards-Campbell Sleep Questionnaire on each of days 2–14, the patient-rated sleep questionnaire completed after day 14, and sleep measurements derived from polysomnography done on days 2–4 and 5–7 (total sleep time, sleep efficiency, REM sleep percentage and arousal index) will all be analysed initially using a Mann-Whitney *U* test to compare the two treatment arms and subsequently using linear mixed models with fixed factors of treatment time and their corresponding interaction, along with random patient effects. ICU LOS, total hospital LOS, mortality and morbidity events will be analysed initially using Kaplan-Meier curves and log-rank tests and subsequently using Cox proportional hazards models. Individuals withdrawn from the study early will be censored at the date of withdrawal. Specific subgroup analysis of major outcomes will be carried out, stratifying by age, sex, delirium medical subgroup and delirium risk as per the prediction of delirium in ICU patients (‘PRE-DELIRIC’) score. A fully specified statistical analysis plan will be finalised and approved by statisticians at the two main hospitals before the database is unlocked and opened. Data analysis is to be carried out using the R software programme [50].

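### The first scheduled sleep rating (RCSQ, Day 1) is probably pre-dose but is left out of the RCSQ analysis, and the day 0 / Day 1 labels must be reconciled before it can serve as a baseline covariate

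*Protocol article*

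**What the plan says.** - **Collection.** Under Sleep quality, the RCSQ is a "daily patient/nurse-rated sleep assessment (Richards-Campbell Sleep Questionnaire) while in ICU". Table 1 ("Time schedule of Pro-MEDIC enrolment, interventions and assessments") marks it on Day 1, Days 2 to 4 and Days 5–14. The Day 1 column also holds informed consent, demographics, co-morbidities and psychiatric history.
- **Dosing.** Patients must "receive the first dose of the study drug on the day of enrolment" (Inclusion criteria). Interventions gives "melatonin 4 mg or placebo at 21:00 for 14 consecutive nights or until ICU discharge".
- **Analysis.** Statistical methods describes "Sleep quality analysis based on the Richards-Campbell Sleep Questionnaire on each of days 2–14". The first-line comparison for every sleep measure is an unadjusted Mann-Whitney test. The follow-on analysis is specified as "subsequently using linear mixed models with fixed factors of treatment time and their corresponding interaction, along with random patient effects". I read the model's fixed factors as treatment, time and treatment by time. No baseline RCSQ term is named.
- **Adjustment elsewhere.** The same paragraph allows adjustment for "important covariates and baseline data where appropriate" in the supporting model of the primary endpoint, and for covariates in the delirium secondary endpoints. The sleep models carry neither phrase.
- **Day labels.** The text of Participant timeline and recruitment puts baseline recording on day 0. Table 1 has no day 0 column, yet its liver function row refers to days 0, 5 and 10.

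**The concern.** If Day 1 is the enrolment day, a rating made before 21:00 describes a night before any study drug. It is then a baseline value of the outcome itself, usually one of the better predictors of later values. The stated analysis uses it in neither the Mann-Whitney test nor the mixed model. The random patient effect does not recover it. That effect models correlation among the records analysed, days 2–14, and the Day 1 record is not among them.

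At stake is precision. Better sleep is a stated secondary objective and the proposed route by which melatonin would act. Polysomnography covers 100 of 850 patients and the other questionnaire is given after ICU discharge, so the RCSQ is the only in-ICU sleep measure planned for everyone. Without the baseline, persistent between-patient differences in sleep stay in the error of the treatment comparison, and any chance imbalance in baseline sleep stays uncorrected.

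**Working it through.** **Is the Day 1 rating pre-dose?** Two readings are possible.

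1. *Day 1 is the enrolment day.* Consent and the baseline items sit under Day 1, and the RCSQ analysis starts at day 2. The first dose is then at 21:00 on Day 1, and a rating of the previous night is pre-dose.
2. *Day 0 is the enrolment day.* The timeline text and the liver function row point this way. The first dose is then at 21:00 on day 0, and a Day 1 rating describes the first treated night.

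The first reading fits more of the document, but the article never says which night the Day 1 RCSQ rates.

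**Is there a figure to reproduce?** None for the RCSQ: the protocol gives no effect, standard deviation or correlation for it. The sample size concerns the primary outcome. It reproduces, 2 × 2.8016² × 45² / 10² = 317.9, or 319 by the t-test version, but has no bearing here.

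**How large is the gain, on the first reading?** All inputs are assumptions: equal correlation rho between any two nights, rho from 0.2 to 0.5; unadjusted power of 80% at two-sided 5%, so the standardised effect is 1.9600 + 0.8416 = 2.8016; and a share p of patients with a usable Day 1 rating.

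- Variance of a mean of m nights, in units of the one-night variance: V = (1 + (m − 1)rho)/m
- Share of that variance explained by one baseline night: R² = rho²/V
- Power after adjustment: Phi(2.8016/√(1 − p·R²) − 1.96)

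Single-day comparison (m = 1, V = 1):

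| rho | R² | power, p = 1 | power, p = 0.7 |
|---|---|---|---|
| 0.2 | 0.040 | 82% | 81% |
| 0.3 | 0.090 | 84% | 82% |
| 0.4 | 0.160 | 86% | 84% |
| 0.5 | 0.250 | 90% | 87% |

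Mean of five nights (m = 5):

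| rho | V | R² | power, p = 1 | power, p = 0.7 |
|---|---|---|---|---|
| 0.2 | 0.36 | 0.111 | 84% | 83% |
| 0.3 | 0.44 | 0.205 | 88% | 86% |
| 0.4 | 0.52 | 0.308 | 92% | 89% |
| 0.5 | 0.60 | 0.417 | 96% | 91% |

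Example, m = 5, rho = 0.3, p = 1: V = (1 + 4 × 0.3)/5 = 0.44; R² = 0.09/0.44 = 0.205; 2.8016/√0.795 − 1.96 = 1.18; power 88%.

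**Interaction.** A treatment-by-time effect is a contrast between nights within a patient. Under equal correlation, the covariance of (night j − night k) with baseline is rho − rho = 0, so a baseline main effect adds essentially nothing to that test.

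**The case against.** The strongest reply is that a full statistical analysis plan is promised, and covariates in a follow-on model of a secondary outcome are usually settled there. One summary sentence covers all the sleep measures, and nothing in it forbids a baseline term. That limits the weight of the point but does not remove it: the article itself fixes the day range and lists the model terms, and it mentions adjustment for other endpoints but not for sleep.

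Second, pre-dose status is inferred. This stands. If day 0 is enrolment, adjusting for the Day 1 rating would condition on a post-treatment value and could remove part of the effect. The labels have to be settled first.

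Third, the size is uncertain. This also stands. Analysis on each day points to the smaller, single-day gains. Equal correlation is doubtful where ratings may come from the patient or the nurse and some patients arrive ventilated and heavily sedated. Enrolment within 48 h of admission means that some may have no ICU night to rate.

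Fourth, the article does plan to examine baseline data for imbalance. That is not adjustment, but imbalance is not ignored.

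A reader might infer that the RCSQ is the trial's main sleep outcome and that a free gain is being thrown away. The documents support neither. Sleep quality is one of seven secondary outcomes, the RCSQ is not ranked first among the sleep measures, and the only label of most important goes to four polysomnography variables, chosen among sleep-study parameters. The gain is low-cost but not free, because missing Day 1 ratings need a rule.

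**Conclusion.** The point holds as a minor improvement. A scheduled RCSQ record, probably taken before the first dose, enters no stated RCSQ analysis. The unadjusted comparisons remain valid, and the loss is of precision in a supporting model. The first-line Mann-Whitney test would not change.

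The figures in the tables show the range and are not an estimate for this trial: they rest on an assumed correlation, an assumed 80% starting power and an assumed share of Day 1 ratings. At a correlation of 0.2 the gain is below 5 percentage points on either comparison.

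The conflict between day 0 and Day 1 holds regardless of any correlation. If Day 1 turns out to follow the first dose, the covariate suggestion falls away, and what remains is that the analysis window omits the first treated night without explanation.

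**What to change.** 1. Reconcile day 0 (timeline text and liver function row) with Day 1 in Table 1, and state which night the first RCSQ rates.
2. If that night precedes the first dose, add the rating as a fixed covariate in the RCSQ linear mixed model. Specify a rule for patients without one, for example mean imputation plus a missing indicator, so that nobody is dropped.
3. If the rating follows the first dose, do not use it as a covariate, and reconcile why the analysis begins at day 2.
4. The order of Mann-Whitney test first and model second may stay. Making the adjusted model the lead comparison is a separate trade-off that this point does not require.

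Cost: wording in Table 1 and Statistical methods or the analysis plan, settled before the database is opened, with no new data. The downside is that some sedated or newly admitted patients will have no usable Day 1 rating, which shrinks the gain.

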**Fig. 1 Fig1:**
[figure not shown]
Time schedule of Prophylactic Melatonin for Delirium in Intensive Care (Pro-MEDIC) enrolment, interventions and assessments. *CAM-ICU* Confusion Assessment Method for the ICU, *CAM-S* Confusion Assessment Method for delirium severity, *ICU* Intensive care unit, *LOS* Length of stay

To allow for accurate recording of LOS, we will allow for a 6-month period after the last patient is enrolled. If there are patients still hospitalised at that point, the last day of the 6-month period will be recorded to calculate as their last day of hospital admission.

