### Data collection and management

Data will be collected and entered into a REDCap© [49] electronic database behind a secure firewall. The REDCap system will perform data entry validation. For the non-primary sites, data can be entered into the REDCap database, or the case report forms can be filled in manually and forwarded to the primary sites. Strict confidentiality and privacy will be kept at all times. The data will be stored in password-protected files and will be kept for 15 years. The final database will be locked after all information for the last patient has been entered and provided to the statistician.

If a participant withdraws consent, the investigators will ask permission to retain all data collected up to the point of withdrawal and to collect survival status and discharge destination data. If subjects cease the study drug for any reason, data will still be collected and interpreted in an intention-to-treat analysis. The reason for withdrawal will be recorded. No attempt will be made to replace patients who withdraw from the study.

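### Secondary length-of-stay and mortality analyses: vital status after withdrawal goes unused, an administrative cut is coded as a discharge, and death is not separated from discharge

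*Protocol article*

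**What the plan says.** Four statements in the protocol article bear on this.

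- **Statistical methods, method.** One plan covers stay, mortality and morbidity: "ICU LOS, total hospital LOS, mortality and morbidity events will be analysed initially using Kaplan-Meier curves and log-rank tests", then "subsequently using Cox proportional hazards models". The text does not say whether a death in ICU or hospital ends the stay, is censored, or competes with discharge.
- **Statistical methods, withdrawal.** The next sentence reads "Individuals withdrawn from the study early will be censored at the date of withdrawal". Mortality is not exempted.
- **Data collection and management.** When consent is withdrawn, the investigators will ask permission "to collect survival status and discharge destination data". Patients who only stop the drug are treated differently: "If subjects cease the study drug for any reason, data will still be collected and interpreted in an intention-to-treat analysis".
- **Participant timeline and recruitment, below Fig. 1.** For stay, "we will allow for a 6-month period after the last patient is enrolled"; for anyone still in hospital then, "the last day of the 6-month period will be recorded to calculate as their last day of hospital admission".

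For context, Objectives names both shorter stay and better mortality as hoped-for effects, Data monitoring and safety expects high baseline mortality without giving a rate, and mortality is read at 28 and 90 days. Full analysis detail is left to a later statistical analysis plan, which is not shown.

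**The concern.** A patient can leave observation by withdrawal, by the calendar cut or by death, and each needs its own handling.

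- **Withdrawal.** Censoring mortality at withdrawal leaves out outcomes that the trial intends to ask for, which sits badly with the intention-to-treat aim. The censoring may also be informative. The Consent section lets patients decide whether to continue once they regain capacity, so those who leave at that step are recovering survivors.
- **Calendar cut.** A patient still in hospital has not been discharged. Recording the cut as the last day of admission makes an incomplete stay look complete, although the chosen methods can handle censoring.
- **Death.** Kaplan-Meier, log-rank and Cox deal with one event at a time, and a hospital stay can end in two ways. With high expected mortality and a hypothesised effect on both outcomes, the result for stay depends on how deaths are coded. The article fixes the method without fixing the coding.

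**Working it through.** The article gives no calculation for stay or mortality. Its only design calculation concerns the primary outcome: 2 × (1.96 + 0.84)² × 45² / 10² ≈ 318 per group, against the stated 319, then inflated to 423. Nothing below changes it. Inputs from the article are 425 per arm and a two-sided 5% level. All rates of mortality, discharge, accrual and withdrawal are assumptions.

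**1. Withdrawal**

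*Deaths at stake*, as 850 × share withdrawing × 90-day mortality, with withdrawers at average risk:
- 2% and 15%: 850 × 0.02 × 0.15 = 2.55, of 127.5 deaths.
- 10% and 25%: 850 × 0.10 × 0.25 = 21.25, of 212.5 deaths.

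Only deaths after withdrawal, with permission given, would be known but unused.

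*Within one arm.* Suppose 5% withdraw at day 7 and all survive, with half of a 20% mortality still to come. Kaplan-Meier survival is 0.90 × (1 − 0.10/0.85) = 0.794 against a true 0.800, so mortality is overstated by 0.6 points.

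*Between arms.* Take a true risk of 20% in both arms and withdrawal of 3% v 7%. As a simple bound, drop withdrawers altogether; the risk in those who stay is (0.20 − w × r)/(1 − w), where w is the share withdrawing and r their risk:
- r = 40%: (0.20 − 0.012)/0.97 = 19.38% v (0.20 − 0.028)/0.93 = 18.49%, a difference of −0.9 points.
- r = 5%: (0.20 − 0.0015)/0.97 = 20.46% v (0.20 − 0.0035)/0.93 = 21.13%, a difference of +0.7 points.
- Equal withdrawal of 5% in both arms: no difference.

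**2. Six-month cut**

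With mean stays of 20 to 40 days (exponential or lognormal) and 24 to 36 months of accrual, about 0 to 2.5 of 850 patients are still in hospital at the cut.

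**3. Death and length of stay**

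*Death counted as end of stay.* Set the discharge hazard at 0.05 per day in both arms, so treatment acts on death only. With in-hospital mortality m, the total exit hazard is 0.05/(1 − m) and the mean stay is (1 − m)/0.05.
- 20% v 15%: means 0.80/0.05 = 16.0 and 0.85/0.05 = 17.0 days. Log exit hazard ratio ln(0.80/0.85) = −0.061; SE √(4/850) = 0.069; chance of a significantly longer stay Φ(−1.96 + 0.88) ≈ 14%. Simulation of 1,500 trials gives 13%.
- 25% v 18%: means 15.0 and 16.4 days; log ratio −0.089; Φ(−1.96 + 1.30) ≈ 25%. Simulation gives 27%.

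The nominal rate in that direction is 2.5%.

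*Three codings compared.* A separate simulation used 400 trials per scenario, 425 per arm, an exit time scale of 20 days and no treatment effect on the discharge hazard. At control mortality 20%, without shared frailty:

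| Coding of death | Death HR 0.7 | Death HR 0.5 |
|---|---|---|
| End of stay | HR 0.94; longer in 14.5% | HR 0.90; longer in 34% |
| Censored | HR 1.00; longer in 2.0% | HR 1.00; longer in 3.0% |
| Kept at risk, never discharged alive | HR 1.11; shorter in 26.5% | HR 1.20; shorter in 72% |

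Percentages are trials significant in the direction shown. Over control mortality of 10-30%, both death hazard ratios, with and without frailty, a significantly longer stay appears in 6.5-69% of trials when death ends the stay and in 1.8-8.0% when it is censored. Monte Carlo SE is up to 2.5 points.

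*What the censored curve shows.* In the same setting at 20% mortality, the discharge hazard is 0.04 and the total hazard 0.05. The Kaplan-Meier median is ln 2/0.04 = 17.3 days (simulated 17.2). The time by which half are discharged alive solves 0.80 × (1 − e^(−0.05t)) = 0.5, so t = 19.6 days (simulated 19.5).

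**The case against.** The strongest reply concerns death. The article states no rule for it, event definitions commonly belong in the analysis plan, and that plan is not shown. If deaths are censored, log-rank and Cox compare cause-specific discharge hazards, which is a recognised competing-risks analysis and close to unbiased here. A reader might infer that any survival benefit from melatonin will make the planned stay analysis biased against it. The documents do not support that: it needs death to count as end of stay, and the article does not say so. Nor are subdistribution or rank-worst methods neutral. With no effect on the discharge hazard they favour melatonin in 26.5% to 72% of trials in the table, because they carry mortality into the comparison. All of this stands. What remains is that single-event methods are fixed for a two-exit outcome with high expected mortality.

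On the cut, the same date would serve for censoring, and few patients are involved. That is right; only the status of the date needs stating.

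On withdrawal, the conflict is narrow. It covers consent withdrawers who give permission, not patients who merely stop the drug, and in a blinded trial with similar withdrawal the bias largely cancels. A reader might also infer that everything needed for a full repair is already collected. It is not: the team seeks survival status and destination, not a later discharge date, so censoring stay at withdrawal is reasonable.

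**Conclusion.** The concern holds with these limits, at minor to moderate severity.

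- **Withdrawal** is the firmest part, because two sections pull against each other. The likely effect is under about 1 percentage point of mortality, given withdrawal of 3% v 7% and a risk in withdrawers of 5% to 40% against 20% overall.
- **The cut** is wrong as worded, but its effect is negligible under the assumed stays and accrual.
- **Death** is a mismatch between method and outcome whose consequence depends on a coding that the article leaves open. It is material if death ends the stay (a one-day difference at 20% v 15% mortality). If death is censored, the fault lies mainly in reading the curve as actual discharge.

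The simulations assume mostly constant hazards, and the article supplies none of the rates.

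**What to change.** 1. In the mortality analyses, follow withdrawn patients to their last known vital status where permission is given, and censor at withdrawal only when status is unknown. Stay may still be censored at withdrawal.
2. State that hospital stays open at the 6-month cut are censored at that date and not counted as discharges.
3. Define the stay outcome as time to discharge alive, with death as a competing event. Show the cumulative incidence of live discharge and of death by arm, compare cause-specific hazards, and add a subdistribution model as a supplement. Report mortality alongside, since subdistribution or rank-worst results also reflect it.

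These are wording changes that can go into the analysis plan before it is finalised. They need no more patients and no follow-up beyond what the article already seeks.

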#### Morbidity and mortality

Standard ICU markers of morbidity and mortality will be recorded on a daily basis until ICU discharge or day 14 after enrolment. These include (1) duration of mechanical ventilation measured as ventilator-free days; (2) daily need for vasopressor use; (3) daily need for renal replacement therapy; (4) re-intubation, delayed extubation or need for tracheostomy; (5) Sequential Organ Failure Assessment score for injury severity; (6) mortality at 28 and 90 days; and (7) destination after ICU discharge.

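### Morbidity events are assigned to Kaplan-Meier, log-rank and Cox although they are recorded only until ICU discharge or day 14, so the method named does not give the proportion of patients with the event

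*Protocol article*

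**What the plan says.** Two sections of the protocol article meet here.

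- **Statistical methods.** Together with ICU and hospital length of stay, "mortality and morbidity events will be analysed initially using Kaplan-Meier curves and log-rank tests", and Cox proportional hazards models follow. The one censoring rule given is "Individuals withdrawn from the study early will be censored at the date of withdrawal". Nothing is said about live ICU discharge or death as an endpoint of observation, and no competing-event method is named.
- **Morbidity and mortality.** "Standard ICU markers of morbidity and mortality will be recorded on a daily basis until ICU discharge or day 14 after enrolment". The list includes "re-intubation, delayed extubation or need for tracheostomy", "daily need for vasopressor use" and "daily need for renal replacement therapy". It also includes "mortality at 28 and 90 days", which is followed beyond the ICU.

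The protocol does not say which listed markers count as morbidity events. Re-intubation and tracheostomy clearly do. Vasopressor use and renal replacement are recorded as a repeated daily status, so they come under this analysis only if they are turned into first-event outcomes.

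**The concern.** Kaplan-Meier treats a censored patient as still at risk, at the same rate as those who remain under observation. A patient who leaves the ICU alive has recovered enough to be at little risk of re-intubation or tracheostomy, and one who dies cannot have the event. If both are censored, the curve estimates how many patients would have had the event had nobody left or died. It does not estimate how many had it.

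The comparison between arms is a separate matter. A shorter ICU stay is among the trial's stated objectives, so differing discharge speed is something the trial hopes to produce. If lower-risk patients leave sooner on melatonin, the remaining risk set is sicker, and a gain in length of stay could show as a worse hazard ratio for morbidity. This bears on safety too. Under Data monitoring and safety, expected complications of critical illness are not reported as serious adverse events unless thought causally related, so the morbidity outcomes are an important place where a difference in organ support would appear.

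**Working it through.** **Figures in the plan.** There is none to reproduce for this point: no morbidity event rate, no power for these outcomes, and no mean or median ICU stay (only an expected stay of at least 72 h). The stated 319 per group is for the primary outcome. It reproduces as 2 × (1.960 + 0.842)² × 45² / 10² ≈ 318, and it plays no part here. Apart from the 425 per arm and the 14-day window, every input below is an assumption.

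**Step 1: constant hazards, discharge and death censored.** Let h be the daily event hazard and o the daily hazard of leaving the ICU.

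- True proportion by day 14: CIF = h/(h+o) × [1 − exp(−14(h+o))]
- Kaplan-Meier version: 1 − KM = 1 − exp(−14h)

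Example with CIF = 10% and mean time to exit of 8 days (o = 0.125): h = 0.0164. Check: 0.0164/0.1414 × [1 − exp(−1.980)] = 0.116 × 0.862 = 0.100. Then 1 − KM = 1 − exp(−0.230) = 20.5%.

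| Mean time to exit (days) | True 14-day proportion | 1 − KM | Ratio |
|---|---|---|---|
| 4 | 10% | 32.8% | 3.3 |
| 6 | 10% | 24.6% | 2.5 |
| 8 | 10% | 20.5% | 2.05 |
| 10 | 10% | 18.2% | 1.8 |
| 14 | 10% | 15.6% | 1.6 |

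Over true proportions of 5% to 30% and the same exit times, the ratio runs from about 1.5 to 3.5.

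**Step 2: events clustered early.** The event hazard now decays with a time constant of 1 to 5 days. The true proportion is 10%, mean time to exit is 4, 5 or 8 days, and exits start either at once or after 2 days. The ratio is then about 1.0 to 2.0. The result depends heavily on when events occur.

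**Step 3: death alone.** Assume 8% with the event, 10% dying first and no discharge. The total cumulative hazard is −ln(1 − 0.18) = 0.198. The event share is 8/18 of that, or 0.088, so 1 − KM = 1 − exp(−0.088) = 8.4%. The excess of 0.4 points compares with a standard error of √(0.08 × 0.92/425) = 1.3 points. Live discharge, not death, causes most of the distortion.

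**Step 4: log-rank and Cox, by simulation, 425 per arm.** A nominal harm signal means z > 1.96, expected in 2.5% of trials.

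- *Same event hazard for every patient, discharge 1.25 or 1.5 times faster on melatonin:* mean z about 0, harm signal 1.8% to 2.4%. No drift.
- *Half the patients sicker (event hazard doubled, discharge hazard halved), the other half the reverse:*
  - All discharge on melatonin 1.5 times faster: mean z +0.32, harm signal 5.4%, although the true proportion falls from 14.7% to 11.9%.
  - Only the less sick leave 1.5 times faster: mean z +0.41, harm signal 6.3%.
  - At 1.25 times faster, these two settings give 3.4% and 3.7%.
- *Stronger contrast:* 30% high risk (median stay 12 days, 25% with the event) and 70% low risk (median stay 4 days, 1% with the event), so 0.3 × 25% + 0.7 × 1% = 8.2% overall in both arms. With low-risk discharge 1.25 or 1.5 times faster on melatonin, the hazard ratio averaged on the log scale is about 1.13 or 1.22, and the harm signal about 8% or 14%.

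**Step 5: equal proportions, shorter stay.** If 10% in each arm have the event but mean time to exit is 6 days on placebo, Step 1 gives h = 0.0202 there. It gives 0.0234 at 5 days and 0.0284 at 4 days. The cause-specific hazard ratios are 0.0234/0.0202 = 1.16 and 0.0284/0.0202 = 1.41, although the proportions are identical.

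**The case against.** The strongest reply is that the protocol never says discharge and death are censored. Its only censoring rule is for withdrawal, and it announces a full SAP, which is not shown. That plan could keep discharged patients event-free to day 14, which would remove most of the overstatement. This stands in part: the censoring is inferred. But it is what Kaplan-Meier does with data that stop at discharge. The method has also been named already, so the point is a named method that does not fit its data rather than missing detail.

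Second, log-rank and Cox with these exits censored validly test the cause-specific hazard. This stands. A reader might infer that faster discharge will make melatonin look harmful. The documents do not support that, because the drift needs discharge speed to be linked to event risk, or equal event proportions despite a shorter stay. With a uniform event hazard there is none.

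Third, a reader might take the overstatement to be about two-fold, or include vasopressors and renal replacement outright. Neither follows. The documents give no rate or stay from which two-fold could be derived, and those two markers are recorded as daily need.

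Fourth, a day-14 proportion has its own weakness: early death lowers it. This stands and is taken into the fix.

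Finally, this is one part of one of seven secondary outcomes, which limits its weight.

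**Conclusion.** The point holds in a limited form. For re-intubation and tracheostomy, and for vasopressors and renal replacement only if they are made first-event outcomes, the recording window and the named method do not fit together. If discharge and death are censored, the direction is clear: 1 minus Kaplan-Meier overstates the proportion with the event. The size is not known from the protocol. Under the assumptions shown it is about 1.0-fold to 3.5-fold.

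The drift towards apparent harm is conditional. In simulated scenarios where discharge is linked to risk and clearly faster on melatonin, the nominal harm signal is about 5% to 14% against 2.5%, with hazard ratios of about 1.13 to 1.22 under the stronger contrast. With milder speeding it stays near 3% to 4%.

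The quoted sentence also covers mortality and length of stay, so a reader might extend the criticism to them. This point does not reach them: mortality is followed to days 28 and 90, and length of stay is not cut off at day 14. The primary analysis and the sample size do not depend on it either.

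**What to change.** In Statistical methods, take morbidity events out of the Kaplan-Meier and log-rank sentence and name which markers count as events. For each, compare the proportion of all randomised patients with the event in ICU by day 14, as a risk difference with confidence interval. The protocol already treats any delirium over the same window as a proportion, with a chi-square test and logistic regression. Read the result beside mortality, because early death lowers this proportion.

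If timing is wanted, report the cumulative incidence function with live ICU discharge and death as competing events, compared by Gray's test. Keep Cox only as a supporting analysis labelled as cause-specific hazards. Leave Kaplan-Meier in place for mortality.

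The cost is a change of wording in the protocol or SAP and standard R functions, with no new data. The downside is that event curves will be lower than Kaplan-Meier curves and competing-risk results are slightly harder to explain.
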